## AIMS OF THE STUDY

*Echis ocellatus* Phase II/III randomised-comparative-trial (**PII/III R-C-T**): to assess and compare the efficacy and safety (incidence and severity of acute anaphylactic reactions) of a ET-Plus, a new antivenom, with ET-G, an antivenom of established efficacy. Both antivenoms achieved adequate efficacy and safety in an open preliminary dose-finding and safety study.

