***Primary end-points***

Proportion of patients given each antivenom whose blood coagulability has been permanently restored 6 hr after the first dose.

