***Sample size***

The trial is designed to demonstrate non-inferiority of ET-Plus compared to ET-G. Based on pre-trial clinical use of ET-G (released for human use on humanitarian grounds because of the lack of any other available antivenom) it was estimated that permanent restoration of blood coagulability at 6 hours would be achieved in 80% of patients in the ET-G group. A 10% non-inferiority margin was deemed acceptable (i.e. at least 70% of ET-Plus patients must have permanent restoration of blood coagulability at 6 hours for it to be deemed non-inferior to ET-G). A sample size of 198 in each group provides 80% power to detect this non-inferiority margin difference of 10%, at a 5% one-sided significance level.

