***Statistical methods***

Baseline characteristics will be described using percentages for categorical variables, means and standard deviations for normally distributed continuous variables or medians and ranges in the case of non-normally distributed continuous variables.

To determine the magnitude and direction of the treatment effects, relative risks and one-sided 95% confidence intervals will be calculated. Continuous outcomes will be checked for normality and the treatment groups will be compared using either the *t* test (for normally distributed data) or the Mann Whitney-U test (for non-normally distributed data). Treatment effects will be presented as a corresponding difference in means or medians (plus one-sided 95% confidence intervals).

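### The one-sided 95% interval rule is worded for all treatment effects with no side named, so it also reaches the comparison of antivenom reactions, for which no directional hypothesis is stated

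*Protocol*

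**What the plan says.** Statistical methods gives the rule in two sentences. The one that matters for reactions, whose incidence is a proportion, is the relative-risk sentence: "To determine the magnitude and direction of the treatment effects, relative risks and one-sided 95% confidence intervals will be calculated". A later sentence extends the same interval type to continuous outcomes: "Treatment effects will be presented as a corresponding difference in means or medians (plus one-sided 95% confidence intervals". Neither sentence limits the one-sided interval to the primary end-point, and neither says whether the limit is an upper or a lower one.

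The Aims section makes safety a comparison alongside efficacy: "to assess and compare the efficacy and safety (incidence and severity of acute anaphylactic reactions) of a ET-Plus, a new antivenom, with ET-G". The section on recording side effects lists early anaphylactic, pyrogenic and late serum-sickness-type reactions.

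A directional hypothesis is stated for one outcome only. The primary end-point is "Proportion of patients given each antivenom whose blood coagulability has been permanently restored 6 hr after the first dose", and Sample size attaches the margin and the one-sided level to it: "A sample size of 198 in each group provides 80% power to detect this non-inferiority margin difference of 10%, at a 5% one-sided significance level". No section gives a direction or a margin for reactions.

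**The concern.** A one-sided limit answers a one-sided question. The primary comparison asks such a question: could ET-Plus be worse than ET-G by as much as the margin? The safety aim does not. It asks how the two products compare, and either could turn out worse. They differ in composition (polyspecific against monospecific) and in initial dose (3 vials against 1). The only reaction figure in the protocol is 0-2 of 6 patients in the preliminary study, which tells the reader very little in advance.

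For such a comparison a reader needs both ends of the interval: the lower end to see whether an excess of reactions on ET-Plus is established, and the upper end to see how large an excess remains compatible with the data. The rule as written supplies only one. That sits badly with its own stated purpose of showing both how large an effect is and which way it points.

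**Working it through.** **1. The plan's own figure.** Inputs from Sample size: 80% restoration on ET-G, margin 10 percentage points, one-sided 5%, 80% power. ET-Plus is also taken as 80%; the protocol does not state this, but it reproduces the stated number.

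n per group = (z₀.₉₅ + z₀.₈₀)² × [p₁(1−p₁) + p₂(1−p₂)] / margin²
= (1.645 + 0.842)² × (0.16 + 0.16) / 0.10² = 197.8, rounded up to 198.

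This matches. One-sided inference is therefore what the primary comparison was designed on, and there is no fault in it there.

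**2. What the rule gives for reactions.** The protocol plans no reaction rates, so those below are assumptions. With n = 198 per arm, p for ET-Plus and q for ET-G:

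SE(log RR) = √[(1−p)/(np) + (1−q)/(nq)]
Limits = RR × exp(±z × SE), with z = 1.960 for two-sided 95% and 1.645 for one-sided 95%.

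Worked case, 26% against 20%:
- RR = 0.26/0.20 = 1.30
- SE = √[0.74/51.48 + 0.80/39.6] = √[0.01437 + 0.02020] = 0.186
- Two-sided: 1.30 × exp(±1.960 × 0.186) = 0.90 to 1.87
- One-sided, lower limit only: 1.30 × exp(−1.645 × 0.186) = 0.96, with no upper limit
- One-sided, upper limit only: 1.30 × exp(+1.645 × 0.186) = 1.77, with no lower limit

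The same formulas over a range of assumed rates:

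| ET-Plus vs ET-G | RR | Two-sided 95% | Lower limit only | Upper limit only |
| --- | --- | --- | --- | --- |
| 10% vs 10% | 1.00 | 0.55 to 1.81 | ≥0.61 | ≤1.64 |
| 20% vs 20% | 1.00 | 0.67 to 1.48 | ≥0.72 | ≤1.39 |
| 33% vs 33% | 1.00 | 0.76 to 1.32 | ≥0.79 | ≤1.27 |
| 26% vs 20% | 1.30 | 0.90 to 1.87 | ≥0.96 | ≤1.77 |
| 20% vs 10% | 2.00 | 1.21 to 3.30 | ≥1.31 | ≤3.05 |

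Two rows show the difficulty. At equal 20% rates, a lower-limit report puts no ceiling on excess reactions, where the two-sided interval stops at 1.48. At 20% against 10%, an upper-limit report reads at most 3.05 and does not show that an excess is established, where the two-sided interval starts at 1.21.

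**3. Is the safety comparison worth reporting fully?** Power at 198 per arm for 10% against 20%, two-sided 5%, with pooled rate 0.15:

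Φ{[0.10 − 1.96 × √(2 × 0.15 × 0.85/198)] / √[(0.09 + 0.16)/198]} = Φ{(0.10 − 0.0703)/0.0355} = Φ(0.83) = 0.80.

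So a trial of this size can say something useful about a difference of that order.

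**The case against.** Four arguments on the other side have weight.

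- **Coverage of reactions is inferred.** Statistical methods does not mention reactions or safety. This is correct, and the point should be held with that reservation. Still, the wording is general, and no other section gives a method for the safety comparison in the aims.
- **No information is lost.** The rule requires the relative risk as well as the limit. On the log scale the estimate and one limit fix the other: from 1.30 and 0.957, SE = ln(1.30/0.957)/1.645 = 0.186, and the two-sided upper limit is 1.30 × exp(1.96 × 0.186) = 1.87. This stands. A reader might infer that the report could never reveal the missing side; the protocol does not support that. The defect is in what is directly reported.
- **An upper limit alone could be defended.** For a new product against an established one, an upper limit on the relative risk of reactions would answer whether the new product could be materially worse. That would be a legitimate design, but the protocol states neither that question, nor that side, nor a margin for it.
- **A statistical analysis plan may settle the side.** It may, and an unnamed side would not by itself be a finding. The interval type, however, is not deferred: the protocol fixes it, and a plan using two-sided intervals for safety would depart from the protocol.

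A further tempting inference is that the rule doubles the chance of a false safety difference, from 5% to 5% + 5% = 10%. That would follow only if the side were chosen after seeing the data and exclusion of 1 were then read as a significance test. The protocol specifies no test or decision rule for reactions, so 10% is not an error rate of the plan.

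**Conclusion.** The point holds as a reporting weakness of moderate to low impact. The interval rule fits the one outcome with a directional hypothesis and is extended by general wording to outcomes without one, including the reaction comparison named in the aims. There it would directly show one end of the interval only, contrary to its stated purpose.

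In the worked illustration the report would carry either at least 0.96 or at most 1.77 in place of 0.90 to 1.87. Those figures rest on assumed rates of 26% and 20%, 198 patients per arm and a Wald interval on the log relative risk. The table shows how they move with other rates; the qualitative result does not depend on the rates chosen. The primary analysis, the sample size and the conduct of the trial are not affected.

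**What to change.** Amend Statistical methods so that the one-sided 95% limit applies only to the primary non-inferiority comparison, with its side named (the lower limit for restoration on ET-Plus relative to ET-G, which is the side that Sample size implies). State that early anaphylactic, pyrogenic and late reactions, and all other secondary outcomes, will be reported with two-sided 95% confidence intervals.

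The cost is a sentence or two of text and slightly wider limits for safety: in the worked case an upper limit of 1.87 rather than 1.77, or a lower limit of 0.90 rather than 0.96. The sample size stays at 198 per group, because it rests on the primary end-point alone. The change can be made at any time before analysis.

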***Ethics***

ET-G and ET-Plus have been developed by the group in collaboration with the manufacturers. They will be imported and given limited registration for clinical trials by NAFDAC. The trial has been sanctioned by NAFDAC and the Gombe State Medical Research Ethics Committee. Informed consent will be obtained from each patient (or their guardian) after they have read the information sheet (in English, Hausa, Tangale and Fulani) and discussed it with medical staff.

## PATIENTS

All patients presenting to Kaltungo General Hospital, Gombe State, Nigeria (June 2005 owards) with a history of snake bite will be reviewed for possible recruitment into the study.

Inclusions: patients of both sexes and any age provided that:

1. they have incoagulable blood as defined by 20WBCT (diagnostic of systemic envenoming by *E. ocellatus* in this geographical area).
2. they have been bitten within the previous 72 hours
3. they or their relatives have given informed consent to admission, treatment and investigation

Exclusions:

1. patients who have already received antivenom for this (recent) snake bite
2. pregnant women
3. patients who are unconscious and/or have lateralising neurological signs indicative of established intracerebral haemorrhage
4. patients with a severe unrelated medical condition such as advanced AIDS or tuberculosis

Patients will be admitted to hospital and kept under observation for at least 48 hours after their blood has become coagulable because of the risk of late recurrence of incoagulable blood and bleeding.

## METHODS

**Diagnosis of the biting species:**

It will be assumed that all patients with incoagulable blood have been envenomed by *E. ocellatus*.This can be confirmed immediately in those cases where the dead snake is brought with the patient.

On admission, history and the results of physical examination will be recorded on a standard proforma (Annex I).

In particular, the following will be noted:

**Local signs:**

• Extent of local swelling (and usually of tenderness):

| **score** | Description |
| --- | --- |
| **1** | Confined to the bitten segment of limb |
| **2** | Extension to mid fore-arm of mid-calf |
| **3** | To knee or elbow |
| **4** | To mid-upper arm or thigh |
| **5** | To shoulder or inguinal ligament |
| **6** | Spreading to trunk |

• Bleeding from fang marks or local incisions

• Blistering

• Bruising

• Necrosis

• Tender, enlarged, painful lymph nodes draining the bitten area

**Systemic signs:**

• Spontaneous systemic bleeding (from gums, nose, skin, gastrointestinal or genitourinary tracts, urine etc)

• Incoagulable blood (20WBCT)

• Shock (supine systolic blood pressure less than 80 mm Hg with impaired peripheral circulation)

• Cardiac arrhythmias

**Follow-up:**

Wherever possible, patients will be encouraged to attend for follow-up assessment 2 weeks after the bite to check for late reactions (serum sickness), subsidence of local swelling, blisters and local necrosis and for any other symptoms.

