## TREATMENT

Antivenom: The initial dose of each antivenom will be the Minimum Effective Safe Dose (MESD), as determined by the preceding PI D-FS: that is 3 vials for ET-Plus and 1 vial for ET-G. This initial dose will be repeated 6 hourly until blood coagulability is restored permanently.

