### Designated “treatment failure”:

If in any patient, given either antivenom fails to achieve permanent restoration of blood coagulability within 24 hours of the first dose and subsequent further 1-3 doses (as required), the case will be designated a “treatment failure” and the patient will given “rescue treatment” with 2 vials of the “gold standard” SAVP (SAIMR) monospecific Echis antivenom.

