**Recurrent envenoming:**

Once blood coagulability has been restored, 20WBCT will be repeated 6 hourly for 48 hours. If the blood becomes incoagulable again, the case will be designated “recurrent envenoming” and more trial antivenom will be given according to the previous schedule.

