## RECORDING OF SIDE EFFECTS OF ANTIVENOM

The following side effects will be recorded:

Within hours

- 1. Early anaphylactic reactions: generalised pruritus, urticarial rash, tachycardia, hypotension, tachypnoea, bronchospasm, angioedema, vomiting, diarrhoea, colicky abdominal pain
  2. Pyrogenic reactions: fever, chills, rigors

Within days/ 1-2 weeks

3. Late serum-sickness-type reactions: generalised pruritus, urticarial rash, arthralgias, peri-articular swellings, fever, lymphadenopathy, mononeuritis multiplex, proteinuria.

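### The only visit for late antivenom reactions is timed from the bite, so in late-entering or re-dosed patients it can fall before the protocol's own 1-2 week serum-sickness window has closed

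*Protocol*

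**What the plan says.** The Follow-up paragraph of the Protocol (under Methods) states that, where possible, "patients will be encouraged to attend for follow-up assessment 2 weeks after the bite to check for late reactions (serum sickness"; the same visit also checks local swelling, blisters and necrosis. No other contact after discharge is described. The only other observation is the hospital stay, which lasts at least 48 hours after coagulability returns.

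The late reactions themselves are defined under the heading "RECORDING OF SIDE EFFECTS OF ANTIVENOM". The time band is "Within days/ 1-2 weeks" and the entry reads "Late serum-sickness-type reactions: generalised pruritus, urticarial rash, arthralgias, peri-articular swellings, fever, lymphadenopathy, mononeuritis multiplex, proteinuria".

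Three other rules determine how long after antivenom the visit falls:

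- Eligibility (Patients): "they have been bitten within the previous 72 hours".
- Repeat dosing (Treatment): "This initial dose will be repeated 6 hourly until blood coagulability is restored permanently". Treatment failure is judged "within 24 hours of the first dose and subsequent further 1-3 doses (as required"), after which rescue antivenom is given.
- Recurrence (Recurrent envenoming): "Once blood coagulability has been restored, 20WBCT will be repeated 6 hourly for 48 hours", with more trial antivenom if the blood becomes incoagulable again.

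**The concern.** The visit and the reaction it is meant to detect run on different clocks. Serum sickness is a reaction to antivenom, so its onset is naturally counted from antivenom. The visit is counted from the bite. Every hour between bite and dose, and between first and last dose, is taken off the time available to see a late reaction. Patients who come late, or who need antivenom again, are observed for the shortest time after exposure.

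What is at stake is the completeness of the late-reaction record. A reaction that starts after the only visit is not captured, and no later analysis can recover days that were never observed.

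**Working it through.** The plan gives no figure of its own here to reproduce; the check is date arithmetic on its rules.

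**Inputs**

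- Visit: day 14 from the bite (Follow-up).
- Bite to first dose, *b*: 0 to 72 h (Patients). The 72 h limit is taken as the latest first dose.
- First dose to a later dose, *d*, from the Treatment, treatment-failure and Recurrent envenoming paragraphs:
  - fourth dose (first plus three more, six-hourly): 3 × 6 = 18 h;
  - rescue point: 24 h;
  - re-dose at the end of the 48 h watch: 6 + 48 = 54 h if blood was restored at 6 h, or 24 + 48 = 72 h if restored at 24 h;
  - last of four doses in a second course: 72 + 18 = 90 h;
  - rescue after a second course: 72 + 24 = 96 h. This assumes that the same schedule, rescue included, applies after recurrence.
- Upper end of the late-reaction band: 14 days, counted from antivenom. The section states no time zero; this is inferred from its heading.

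**Formula**

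Days from dose to visit = 14 − (*b* + *d*)/24. Uncovered days = 14 minus that result = (*b* + *d*)/24.

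**Results** (days from dose to visit, uncovered days in brackets)

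| Dose | *b* = 0 h | *b* = 12 h | *b* = 24 h | *b* = 72 h |
|---|---|---|---|---|
| First dose | 14.0 (0) | 13.5 (0.5) | 13.0 (1.0) | 11.0 (3.0) |
| Fourth dose, +18 h | 13.25 (0.75) | 12.75 (1.25) | 12.25 (1.75) | 10.25 (3.75) |
| Rescue point, +24 h | 13.0 (1.0) | 12.5 (1.5) | 12.0 (2.0) | 10.0 (4.0) |
| Recurrence dose, +54 h | 11.75 (2.25) | 11.25 (2.75) | 10.75 (3.25) | 8.75 (5.25) |
| Recurrence dose, +72 h | 11.0 (3.0) | 10.5 (3.5) | 10.0 (4.0) | 8.0 (6.0) |
| Last of second course, +90 h | 10.25 (3.75) | 9.75 (4.25) | 9.25 (4.75) | 7.25 (6.75) |
| Rescue after recurrence, +96 h | 10.0 (4.0) | 9.5 (4.5) | 9.0 (5.0) | 7.0 (7.0) |

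Entry at 72 h alone leaves 3 of the 7 days of the second week uncovered (3/7 = 43%). Entry at 72 h plus one recurrence dose at +72 h leaves 6 of 7 (86%). Late entry is not required: a patient dosed at once and re-dosed at +72 h is seen 11 days after that re-dose. At the other end, a patient dosed within 12 h and not re-dosed loses at most half a day.

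**Possible difference between arms**

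Repeat doses within the first course shorten follow-up after the last dose by at most 18/24 = 0.75 day. A recurrence dose shortens it by up to 72/24 = 3 days. The protocol gives no recurrence rates. If, for illustration only, the arms differed in recurrence by 5 to 20 percentage points, mean follow-up after the last dose would differ by about 0.05 × 3 = 0.15 day to 0.20 × 3 = 0.6 day.

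**The case against.** There is a fair case for leaving the visit alone. The side-effects section names no time zero and its band is loose, so a visit 8 to 11 days after dosing still lies inside it; this is not a direct contradiction. Counting from the last dose rather than the first is a further choice. Counted from the first dose, the loss never exceeds 3 days. The 8-day case stacks three extremes: entry at the limit, restoration only at 24 h, and recurrence at the end of the watch. The bite is also a sensible origin for the local signs checked at the same visit, and attendance is voluntary, so non-attendance is probably the larger loss.

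All of this limits the size of the point. It does not remove the mismatch: serum sickness is the first stated purpose of the visit, and nothing later would catch a reaction that the visit precedes.

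A reader might infer three stronger things that the documents do not support:

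- That second-week reactions are missed in general. Only onsets after the visit are lost; earlier ones can be seen in hospital or reported at the visit.
- That 8 to 11 days is the usual interval. It is what can happen to late-entering patients. The protocol gives no bite-to-dose times, and 8 is not the floor either.
- That the arm needing more re-dosing will look falsely safer. Presentation delay precedes randomisation and should balance. Re-dosing could differ by arm, but it leaves the interval from the first dose unchanged, and its effect on follow-up after the last dose is possible, unquantified and likely small.

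**Conclusion.** The point holds as a gap in observation for some patients. Followed as written, the visit can fall 11 days after the first dose and, with late entry plus recurrence, about 7-8 days after the last dose, leaving 3 to 7 days of the protocol's own late-reaction band unobserved. This assumes that the band is counted from antivenom and that the patient attends on day 14.

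The share of patients affected cannot be derived from the protocol. The primary end-point is coagulability at 6 hours, and the safety aim in Aims of the Study is defined by acute anaphylactic reactions, so neither the non-inferiority conclusion nor the stated safety comparison depends on this visit. It is a cheap improvement, not a threat to the trial.

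**What to change.** In the Follow-up paragraph, time the same single visit from the last dose of antivenom, counting any recurrence or rescue dose, with a bounded window such as 14 to 17 days after it. The upper bound matters: a minimum alone would not give patients a comparable period of observation. State the same time zero in the side-effects section.

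Set the appointment at discharge from the dose dates and times already on the proforma (Annexe 1). Record the visit date explicitly, because the progress sheet has a date row but is not assigned to this visit. Report late reactions by arm among those who attend.

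The cost is one amended sentence and one recorded date. Compared with day 14 from the bite, the start of the window moves by almost nothing for a patient treated promptly and by up to about 6-7 days at the extreme. A later date may lose a little attendance. Bite-to-visit timing also becomes less uniform for the local signs, with the window opening 14 to 21 days after the bite (14 + 7 at the extreme). No dosing, re-dosing or rescue rule is altered.

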**LABORATORY TESTS**

Incoagulable blood will be defined by the simple 20-minute whole blood clotting test (20 WBCT). Two ml of venous blood is placed in a new, clean, dry glass test tube and left for 20 minutes at room temperature. The tube is then tipped up to see if the blood runs out or has clotted.

Restoration of blood coagulability as estimated by the whole blood clotting test, will be taken as evidence of the efficacy of the antivenom. Persistence of incoagulable blood, measured by the 20WBCT (Sano-Martins et al, 1994), six hours after the first dose of antivenom will be an indication for repeating the initial dose.

